## Abstract

**Background:**

Transcatheter arterial embolization (TAE) has long been used for hemostasis of traumatic or postoperative hemorrhage and embolization of tumors. Previous retrospective studies of TAE for painful bone metastases showed 60%–80% pain reduction with a median time to response of 1–2 days. Compared with radiotherapy and bisphosphonates, time to response appeared earlier than that of radiotherapy or bone-modifying agents. However, few prospective studies have examined TAE for this indication. Here, we describe the protocol for a confirmatory study designed to clarify the efficacy and safety profile of TAE.

**Methods:**

This study will be a multicenter, single-arm confirmatory study (phase 2–3 design). Patients with painful bone metastases from any primary tumor are eligible for enrollment. TAE will be the main intervention. Following puncture of the femoral artery under local anesthesia and insertion of an angiographic sheath, angiography will confirm that the injected region includes tumor vasculature. Catheter position will be adjusted so that the embolization range does not include non-target tissues. Spherical embolic material will then be slowly injected into the artery to embolize it. The primary endpoint (efficacy) is the proportion of subjects with pain relief at 72 h after TAE and the secondary endpoint (safety) is the incidence of all NCI Common Terminology Criteria for Adverse Events version 5.0 Grade 4 adverse events and Grade ≥ 3 necrosis of the central nervous system.

**Discussion:**

If the primary and secondary endpoints are met, TAE can be a treatment choice for painful bone metastases. Trial registry number is UMIN-CTR ID: UMIN000040794.

**Trial registration:**

The study is ongoing, and patients are currently being enrolled. Enrollment started in March 2021. A total of 36 patients have participated as of Aug 2022.

Protocol Version: Ver1.4, 13/07/2022.

## Background

As life expectancy increases due to recent advances in cancer treatment, and the number of cancer patients increases due to an increase in cancer incidence resulting from an increase in patients surviving stroke and other cardiovascular disease, the number of patients with bone metastases is also increasing [1]. It is reported that approximately 75% of bone metastases are painful [2].

For patients with painful bone metastases, there are different approaches to pain relief. Among current standard treatments, time to pain relief is 4 to 8 weeks in most patients receiving radiotherapy [3, 4] and 1 to 3 months in responders to bone-modifying agents [5] (30% of treated patients). Surgery improves symptoms quite rapidly, but is indicated for limited pathologies and is often unfeasible due to its invasiveness, depending on the patient’s general condition [6]. Analgesics, including opioids, temporarily relieve pain but do not remove its cause.

Arterial embolization is used for hemostasis of traumatic or postoperative hemorrhage and for embolization to reduce tumor size by ischemia. Previous retrospective studies of arterial embolization for painful bone metastases [7–11] showed pain reduction of 60%–80% with a median time to response of 1–2 days. Compared with radiotherapy and bone-modifying agents, this reported time to response is faster. Although arterial embolization with a mixture of thrombotic and chemotherapeutic agents, such as trans-arterial chemoembolization (TACE) for hepatocellular carcinoma, is a commonly used technique, few prospective studies have evaluated transcatheter arterial embolization (TAE) without chemotherapeutic agents for painful bone metastases.

Here, we report the protocol for a confirmatory study of TAE, which aims to clarify the efficacy and safety profiles of this treatment.

## Methods

### Study design

The purpose of this study is to clarify the efficacy and safety profile of TAE for painful bone metastases. This study is a collaboration between the Japan Interventional Radiology in Oncology Study Group (JIVROSG) and the Japan Supportive, Palliative, and Psychosocial Oncology Group (J-SUPPORT). This protocol has been reviewed by the J-SUPPORT Scientific Advisory Board, and approved as a JIVROS/J-SUPPORT1903 study (PALEM study).

### Patient and public involvement

Cancer survivors and nonmedical persons were invited to attend the scientific advisory board meeting of J-SUPPORT. From protocol concept to writing the informed consent document, they participated in our discussion. Scientific advisory board members are listed on the following web page: Committees and Administrative Office | J-SUPPORT.

### Study setting

This study is a multicenter, single-arm confirmatory study to clarify the efficacy and safety profile of TAE for painful bone metastases (phase 2–3 design).

All participants will be recruited from 24 hospitals: Aichi Medical College, Aichi Cancer Center, Iwate Medical College, Cancer Institute Hospital of JFCR, Tonan Hospital, National Cancer Center Hospital, National Cancer Center Hospital East, Shizuoka Cancer Center, Juntendo Hospital, Teina Keijinkai Hospital, Hokkaido University Hospital, Ryukyu University Hospital, Osaka University, Kobe University, Keio University, Saiseikai Fukuoka Sogo Hospital, Nara City Hospital, Hakodate Goryokaku Hospital, Hyogo Cancer Center, Hyogo Medical University, Fukuchiyama City Hospital, Nara Medical Hospital, St. Marianna University Hospital, and Hokkaido Cancer Center.

The protocol treatment will be performed on inpatients.

To ensure the safety of subjects, registration will be suspended to evaluate safety once 20 subjects are recruited. In the exploratory phase, if any CTCAE Grade 4 adverse event or a Grade 3 or higher adverse event of central nervous system (CNS) necrosis occurs in at least 4 of the 20 subjects, the study will be discontinued (stopping rule) (Fig. 1).

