**Fig. 1 Fig1:**
[figure not shown]
Study schema this study consists of two sections, the exploratory and confirmatory phases. Registration will be suspended when 20 subjects are recruited to analyze the data set rather than investigate all the events individually. (Stopping rule) Recruitment of a total of 120 patients is planned

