### Safety (secondary endpoint)

The secondary endpoint (safety) is the incidence of all CTCAE Grade 4 adverse events and CTCAE Grade ≥ 3 CNS necrosis associated with the arterial embolization procedure.

In this study, the incidence of all CTCAE Grade 4 adverse events and CTCAE Grade ≥ 3 CNS necrosis associated with the arterial embolization procedure will be assessed in the 2-week post-TAE observation period.

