#### Proportion of subjects with a complete response

To demonstrate that TAE is more effective than placebo, the proportion of complete responders will be assessed.

The proportion of complete responders will be calculated using the following equation:4$$proportion of complete responders = complete response/(FAS - subjects with missing data)$$

The definition of an analysis set is the population of subjects enrolled in the study, excluding those who are doubly or wrongly registered (Table 1).

**Table 1 Tab1:** The definition of each analysis set

Analysis set	Definition
All enrolled subjects	Population of subjects enrolled in the study, excluding those who are doubly or wrongly registered
Full analysis set (FAS)	Population of all enrolled subjects, excluding the following subjects:
	● Subjects who are found ex post facto to be ineligible (fail to meet all of the eligibility criteria or meet any of the exclusion criteria) based on information obtained in accordance with the protocol
	● Subjects who are found to be ineligible based on information obtained after enrollment or unscheduled examination results
	● Subjects who have never received transcatheter arterial embolization (non-implementation)
	● Subjects from whom no data have been collected after enrollment, except information at enrollment into the study
Safety analysis set (SAS)	Population of all enrolled subjects who have been treated with arterial embolization at least once
Per protocol set (PPS)	Population of subjects in the FAS who are in compliance with the protocol

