### Participant timeline

Patients will be registered online before the TAE protocol is initiated.

After protocol treatment starts, several evaluations for pain and a general examination will be performed at 24 h, 72 h, 7 days, and 14 days after protocol treatment. The assessment schedule from enrollment to 2 weeks after protocol treatment is shown in Table 2.

**Table 2 Tab2:** Time Schedule

	Pretreatment	Arterial embolization	24 h (± 3 h)	72 h (± 3 h)	7 d (± 1 d)	14 d (± 2 d)
Karnofsky Performance Status (KPS)	〇		〇	〇	〇	〇
Numerical rating scale (NRS)	〇					
Brief Pain Inventory			〇	〇	〇	〇
Quantity of morphine used per day	〇		〇	〇	〇	〇
Blood exam	〇		〇			
CTCAE ver 5.0 (safety profile)		〇	→ always checked →			〇

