### Sample size

The clinical hypothesis is that patients with painful bone metastases can be safely treated with arterial embolization for immediate pain relief.

The early response rate after arterial embolization must exceed that after radiotherapy in order for arterial embolization to be established as a new palliative therapy. Since the early response rate was reported to be 26% at 1 week after radiotherapy [16], it is assumed to be lower at 72 h after radiotherapy.

Assuming that the threshold for the proportion of subjects with pain relief at 72 h after arterial embolization, i.e., the primary efficacy endpoint, is 26%, and the expected response rate is 40%, which represents the minimum clinical utility, at least 113 patients are required to provide a power of 90% at a one-sided significance level of 2.5% (normal approximation test).

On the other hand, an adverse event associated with TAE, which is the primary safety endpoint, is defined as any CTCAE Grade 4 adverse event or Grade ≥ 3 CNS necrosis. As described in “Common Adverse Events Associated with Arterial Embolization,” adverse events (including mild events) have been reported in 5% to 7% of patients who undergo arteriography, 10% of patients treated with arterial embolization, and approximately 15% of patients treated with TACE. Considering that patients in poor general condition will be included in this study, the unacceptable threshold incidence for the clinical use of this treatment is set at 15%, equal to that for TACE for hepatocellular carcinoma [17]. Assuming that the incidence will actually be approximately 5% in this study where no anticancer drugs will be used concomitantly; and that bones will be treated, at least 96 patients are required to provide a power of 90% at a one-sided significance level of 2.5% (normal approximation test) (Fig. 1).

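### The early safety stopping rule is set on 20 recruited subjects rather than 20 embolised ones, which makes it slightly less likely to stop if any of the 20 are never treated

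*Protocol article*

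**What the plan says.** Study setting in the protocol article fixes both the trigger and the denominator of the rule. The trigger is that "registration will be suspended to evaluate safety once 20 subjects are recruited". The rule is that if a Grade 4 event, or central nervous system necrosis of Grade 3 or higher, "occurs in at least 4 of the 20 subjects, the study will be discontinued (stopping rule"). The legend of Fig. 1 repeats the recruitment trigger: "Registration will be suspended when 20 subjects are recruited to analyze the data set rather than investigate all the events individually".

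Four other places bear on who those 20 are:

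- Participant timeline: "Patients will be registered online before the TAE protocol is initiated".
- Table 1, among the exclusions from the full analysis set: "Subjects who have never received transcatheter arterial embolization (non-implementation").
- Table 1, definition of the Safety Analysis Set (SAS): "Population of all enrolled subjects who have been treated with arterial embolization at least once". Statistical methods of analysis bases the final safety decision on this set.
- Safety (secondary endpoint): the events "will be assessed in the 2-week post-TAE observation period".

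The article does not say that the 20 must have been embolised, and it gives no data cut-off for the review.

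**The concern.** A subject can be recruited and then not embolised. The Intervention section makes embolisation depend on angiography showing tumour stain and no vessel in which it is contraindicated, and that check comes after registration. Such a subject fills one of the 20 places without having had the treatment under test. The boundary is a count, not a proportion of those treated, so it does not adjust. The interim gate and the final safety test also describe the same kind of event in different populations.

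The Discussion relies on strict thresholds and stopping rules to protect the reliability of a trial without a control arm. The exposed denominator of the only early safety gate should therefore be fixed.

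**Working it through.** **Inputs.** The rule is 4 or more events in 20 (Study setting). Under Sample size, "the unacceptable threshold incidence for the clinical use of this treatment is set at 15"%, and the expected incidence is about 5%. The number of the 20 who are never embolised is not given; 0, 1 and 2 are assumed here.

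**The plan's own figure.** The article states no stopping probabilities for the rule. The nearest stated figure is the safety sample size of 96 (15% against 5%, one-sided 2.5%, power 90%, normal approximation):

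n = [z(0.975)·√(p0(1−p0)) + z(0.90)·√(p1(1−p1))]² / (p0−p1)²

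= [1.960·√(0.15·0.85) + 1.282·√(0.05·0.95)]² / 0.10² = 95.87, rounded up to 96.

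This matches, so 15% and 5% are the incidences that the design works with.

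**Stopping probability.** With m embolised and fully observed subjects, true incidence p, and no events in the other 20−m:

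P(stop) = 1 − Σ C(m,k)·p^k·(1−p)^(m−k), summed over k = 0 to 3.

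For m = 20 and p = 0.15: 1 − (0.0388 + 0.1368 + 0.2293 + 0.2428) = 0.352.

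| Embolised among the 20 | true 5% | true 15% | true 20% |
|---|---|---|---|
| 20 | 0.016 | 0.352 | 0.589 |
| 19 | 0.013 | 0.316 | 0.545 |
| 18 | 0.011 | 0.280 | 0.499 |

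At 15% the loss is 0.352 − 0.316 = 0.036 with one untreated subject and 0.352 − 0.280 = 0.072 with two. At 20% it is 0.589 − 0.545 = 0.044 and 0.589 − 0.499 = 0.090.

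**Sensitivity to the form of the assumption.** Suppose instead that each of the 20 is embolised with probability 0.95 or 0.90, so that events follow a binomial with n = 20 and rate 0.95p or 0.90p. P(stop) is then 0.3161 or 0.2805 at 15%, and 0.5439 or 0.4974 at 20%. The picture is the same.

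**Why these are upper bounds on the loss.** The table gives non-embolised subjects no risk at all. A subject who has had femoral puncture, catheterisation and contrast can have a procedural event; Sample size itself cites adverse events, including mild ones, in 5% to 7% of patients having arteriography. The rule in Study setting also counts Grade 4 events without requiring a link to the procedure, whereas the safety endpoint requires one. Either route lets a non-embolised subject contribute to the count.

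**The case against.** The strongest objection concerns timing. A reader might infer that the rule is applied on the day the 20th subject is registered, so that subjects still inside their two-week window also dilute the count. The article does not say so. Registration is suspended so that safety can be evaluated and the data analysed, and a pause is exactly what lets follow-up mature. The cut-off is unstated, and a condensed article may leave it to the full protocol. That objection stands: timing is something to state, not an error.

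Second, the size rests on an assumed rate. This also stands. The article calls the procedure not technically difficult, and nothing in it supports non-treatment as high as one in five. At 16 embolised subjects the stopping probability would be 21% at a true 15% and 40% at a true 20%, but those figures should not be presented as likely. Nor can the rule be called laxer than the plan claims, since the plan claims no operating characteristics.

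Third, an interim count and a final confidence interval are different decisions and need not share a denominator. That is fair as far as it goes: the difference is not a contradiction. It does not answer the point that a gate meant to judge the treatment is counted on people who may not have received it.

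Fourth, counting only embolised subjects could hide a serious access or contrast complication in someone whose procedure was abandoned. This is a sound warning, and the fix below allows for it.

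Last, Trial registration reports 36 participants by August 2022, so the gate has probably been passed. A new definition can no longer govern that decision, but it can make the report of it clear.

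**Conclusion.** The point holds on the denominator. The stopping rule is stated for recruited subjects, although the article itself separates recruitment from treatment, foresees enrolled subjects who are never embolised, and judges final safety on treated subjects. With a fixed count of 4, the error runs mainly toward not stopping.

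The effect is modest. With 1 or 2 of the 20 not embolised, and no events in them, the stopping probability falls by at most about 4 or 7 percentage points at a true 15%, and about 4 or 9 points at a true 20%. Both the rate and the absence of events are assumptions.

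It would be wrong to attribute the rule's limited sensitivity mainly to the denominator. Even with 20 treated and fully observed subjects, it stops only 35% of the time at the incidence that the article calls unacceptable.

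**What to change.** Define the safety cohort as the first 20 subjects in the SAS, that is, embolised at least once. Evaluate the rule once all 20 have completed the 14-day assessment or have died or withdrawn. Leave the count of 4 unchanged. Add that qualifying events in subjects who began the procedure (puncture or angiography) but were not embolised are still reported to, and considered in, the safety review.

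Because the gate has probably been passed, also report:

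- how many of the first 20 recruited subjects were embolised and fully observed;
- the qualifying event count in the first 20 SAS subjects, labelled as a clarification and not as a re-run of the decision;
- any qualifying events in subjects who began the procedure but were not embolised.

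The cost is a sentence or two of protocol text and a short tabulation. Applied prospectively, the definition would mean a slightly longer pause and possibly one or two more registrations before it.

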**Fig. 1 Fig1:**
[figure not shown]
Study schema this study consists of two sections, the exploratory and confirmatory phases. Registration will be suspended when 20 subjects are recruited to analyze the data set rather than investigate all the events individually. (Stopping rule) Recruitment of a total of 120 patients is planned

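### The safety boundary appears to be read only once, at 20 recruited subjects; the article does not say that registration halts if a 4th confirmed event comes earlier

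*Protocol article*

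**What the plan says.** The Study setting section of the protocol article gives subject safety as the aim and places the evaluation at a fixed enrolment count: "registration will be suspended to evaluate safety once 20 subjects are recruited". The next sentence, which opens by referring to the exploratory phase, gives the boundary: a Grade 4 event or Grade 3 or higher CNS necrosis that "occurs in at least 4 of the 20 subjects, the study will be discontinued (stopping rule").

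The Fig. 1 legend describes the purpose and manner of the pause: "Registration will be suspended when 20 subjects are recruited to analyze the data set rather than investigate all the events individually".

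Two other places bear on the point. Table 2 shows CTCAE events being checked continuously after embolization, but no halt is attached to that. Data collection methods provides for central monitoring through the EDC system. The section Safety (secondary endpoint) sets a 2-week observation period after the procedure.

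**The concern.** The rule is a fixed count out of a fixed 20 subjects. The number of validly registered subjects with a confirmed event can only rise, so the fourth such subject settles the outcome whenever that subject appears. If the boundary is consulted only at 20, anyone treated in between undergoes an invasive procedure in a study whose own rule already requires it to stop, and their results have no bearing on that decision.

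What is at stake is the protection of the exploratory-phase subjects in the situation the rule exists for, a true event rate above the expected one. The Discussion also relies on strict thresholds and stopping rules to support an uncontrolled confirmatory design, so the rule should be unambiguous to all 24 hospitals and the data center.

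**Working it through.** **Inputs.** From Study setting: look at n = 20, boundary 4. From Sample size: unacceptable rate 15%, expected rate 5%, one-sided 2.5%, power 90%, safety N = 96; efficacy 26% against 40%, N = 113. The rates 20%, 30% and 40% are not in the document; they are assumptions added to show a range.

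**The plan's own figures.** One-sample normal approximation:

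N = [z(0.975)·√(p0(1−p0)) + z(0.90)·√(p1(1−p1))]² / (p1−p0)²

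- Safety: (1.960 × 0.3571 + 1.2816 × 0.2179)² / 0.10² = 95.87, rounded up to 96. This agrees with the article.
- Efficacy: (1.960 × 0.4386 + 1.2816 × 0.4899)² / 0.14² = 112.90, rounded up to 113. This agrees too.

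The article gives no operating characteristics for the 4-of-20 rule, so there is no stated figure to reproduce for it.

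**When the 4th event occurs.** For a true rate p, the probability that the 4th subject with an event is subject k is

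P(K = k) = C(k−1, 3)·p⁴·(1−p)^(k−4), for k = 4, …, 20.

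Summing over k = 4 to 20 gives P(4 or more events in 20), the chance of discontinuation. Summing over k = 4 to 19 gives the chance that the boundary is met before subject 20. The mean of K, given that the boundary is met, gives the average number of subjects still to come, 20 − E[K | met]. Multiplying that by the chance of discontinuation gives the average over all trials.

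| True rate | P(discontinue) | P(met before subject 20) | Mean subject at 4th event, if met | Subjects after it, if met | Subjects after it, all trials |
|---|---|---|---|---|---|
| 5% (expected) | 0.016 | 1.3% | 16.3 | 3.7 | 0.06 |
| 15% (unacceptable) | 0.352 | 31.6% | 15.0 | 5.1 | 1.8 |
| 20% (assumed) | 0.589 | 54.5% | 14.1 | 5.9 | 3.5 |
| 30% (assumed) | 0.893 | 86.7% | 12.0 | 8.0 | 7.2 |
| 40% (assumed) | 0.984 | 97.7% | 9.8 | 10.2 | 10.0 |

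Last column, for example: 0.0159 × 3.70 = 0.06 and 0.3523 × 5.05 = 1.8.

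**Effect of reading the boundary as events accrue.** The sum of P(K = k) over k = 4 to 20 equals the binomial tail at 20 for every p (for example 0.3523 both ways at 15%). The two ways of reading the boundary therefore lead to the same decision in every possible sequence of events, and the P(discontinue) column applies to both.

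**Direction of error.** The calculation treats each event as known and confirmed before the next subject is treated. With a 2-week observation period, some later subjects would already have been treated. As a rough guide, 36 subjects between March 2021 and August 2022 (about 17.5 months) is 36 / 17.5 ≈ 2.1 per month, or about one subject per 2 weeks. That is an overall average including any suspension, and the pace in the first 20 may have differed.

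**The case against.** The strongest reply is textual. The discontinuation sentence refers to the exploratory phase as a whole and is not itself tied to the pause, so it can be read as operating as soon as a fourth subject has an event. On that view the legend merely explains, in awkward English, that the pause reviews aggregate data. This stands in part: a reader might infer that the protocol instructs sites to keep enrolling after four events, even if the first four subjects all had one. The document does not say that. Nor does it show sites applying the boundary themselves, since registration is online and monitoring is central. What remains is that the evaluation is dated to 20 subjects, the legend contrasts it with looking at events individually, and nothing in the article provides for an earlier halt.

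Second, the article condenses a fuller protocol that may contain serious-event review or an interim halt. That is possible and limits confidence. The point, however, rests on what the article states about timing and manner, not on the absence of such procedures.

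Third, a running count can be revised. The safety endpoint counts events associated with the procedure, a qualifier that the discontinuation sentence omits, and Table 1 removes doubly or wrongly registered subjects. This stands: the outcome is settled only by confirmed events in valid subjects.

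Fourth, at the expected 5% rate the effect is negligible, and the 20-subject look should have passed by August 2022. Both are true. The first describes the case in which a stopping rule is not needed; the second changes what can usefully be done now.

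**Conclusion.** The point holds in limited form. Read together, the two passages describe one look at 20 subjects and leave an earlier crossing of the boundary unaddressed or, at best, ambiguous. At the protocol's unacceptable rate of 15% there is about a one-in-three chance (31.6%) of meeting the boundary before subject 20, with on average 5.1 subjects following when it is met and 1.8 averaged over all trials. At 5% the matter is almost absent (1.3%; 0.06 subjects). At the assumed rates of 20% to 40% the conditional number is 5.9 to 10.2. All these are upper estimates and rest on independent events with a common rate, each known before the next treatment.

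A reader might also infer that the error rates or the sample size are at fault. They are not: the figures of 96 and 113 reproduce, and the chance of discontinuation is the same either way. This is a matter of subject protection and clear wording, not of the validity of the final tests.

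**What to change.** Leave the boundary of four and the event definition as they are. Reword Study setting and the Fig. 1 legend so that they say the same thing: the boundary is read cumulatively, and registration is suspended at the 4th subject with a confirmed qualifying event or at the 20th subject, whichever comes first. Drop the legend's contrast with individual events, or explain what it means.

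The cost is a running central count of qualifying events, for which the EDC and central monitoring are already in place, and possibly a pause in registration while an event is confirmed. There is no cost in error rates or power.

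Since 36 subjects had participated by August 2022, the change of wording can no longer protect the first 20. The trial report should therefore state when qualifying events occurred among those subjects, in order of enrolment, when registration was suspended, and how the rule was applied.
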